### Outcome measures

The primary outcome measure will be the incidence of new falls, fallers, based on the Falls Calendar. Secondary outcome measures will be fall-related injuries, generic health-related HRQoL, compliance, quality adjusted life years (QALY), genetic polymorphisms associated with increased adverse drug reactions, and positive or negative health effects, cost, and cost-effectiveness.

### Measurements

### Medication use

Medication use will be assessed by registering the drug names directly from the medication packaging. For each drug, both prescription and over-the-counter (OTC), the name, intake frequency, dosage, start and stop dates, and whether the drug was prescribed before or after the fall will be registered. The information will be verified and compared with data retrieved from the patients' General Practitioner and local pharmacist.

### Quality of life

The level of independency of the activities of daily living (ADL) will be examined using the Barthel Index (ranging from zero for full independency to 20 for full dependency) [26]. Quality of life will be measured using the Dutch version of the SF-12 and EQ-5D (EuroQol) questionnaire. The EQ-5D has been designed by the Euro-HRQoL Group to assess the experienced general quality of life in large populations in order to provide a simple, generic measure of health for clinical and economic appraisal [27]. The EQ-5D questionnaire covers five health domains (mobility, self-care, usual activities, pain/discomfort, and anxiety/depression) and a Visual Analogue Scale (VAS) to record the current experienced health status. The EuroQol (EQ-5D) is a validated and extensively used general health questionnaire to measure quality of life [28,29]. It is recommended for the assessment of HRQoL in trauma patients, especially for economic assessments [30]. The SF-12 contains 12 questions and has been designed and validated to assess the quality of life in large population studies [31,32]. Fall-risk will be assessed using a validated FRP [33]. The FRP contains five questions, two measurements (handgrip strength and body weight), and two interacting items. Hand grip strength will be measured using a digital strain-gauged dynamometer (Takei TKK 5401, Takei Scientific Instruments Co, Ltd., Tokyo, Japan). Body weight will be measured with a calibrated beam scale. For each item points are scored and summed (range 0-30), where zero represents a low risk of recurrent falling and 11 and over indicates a high risk of recurrent falling (2 or more falls in the next 12 months) [33].

### Physical performance

In order to assess the physical activity, three tests will be conducted. First, the chair stand test, which is a standardized test in which the participant stands up and sits down five consecutive times. The patient is not permitted to use the chair's arms supports during standing up or sitting down [34]. The Timed Up-and-Go test (TUG-test) will be conducted, in which the participant has to stand up from sitting position and walks three meters along a line, perform a 180 degree turn and walk back to the chair and sit down [34]. A tandem stand test will be used in order to assess balance. The test will be performed in standing position, in which the patient has to stand fully independently for 10 seconds with both feet in front of each other, and is scored as correct or failed. All three mobility tests are conducted twice, and the best time (where appropriate) will be used.

Orthostatic hypotension will be measured by using a calibrated sphygmomanometer, in supine position followed by five minutes standing straight up. The blood pressure will be measured in supine position and after one, two, three, four, and five minutes standing. The blood pressure is registered in millimetres of mercury (mmHg), heart rate in beats per minute. Orthostatic hypotension is defined as a decrease of 20 mmHg systolic or a decrease of 10 mmHg diastolic in standing position [35].

### Costs

The total direct and indirect costs of both fall-risk increasing drugs withdrawal and 'care as usual' will be measured. All analysis will be performed in accordance with Dutch guidelines for economic evaluations [36]. Direct healthcare costs include the additional costs of the systematic fall-related drugs assessment and modification, drug consumption (including the costs for substitution drugs), and fall-related and non-fall-related healthcare consumption during one year of follow-up (e.g. General Practitioner, outpatient visits, and hospital admissions).

Real medical costs are calculated by multiplying the volumes of health care use with the corresponding unit prices. For the intervention (systematic fall-related drugs assessment) the full cost price will be calculated and for the other health care costs standard cost prices will be used as published by Oostenbrink [36]. The full cost price of patient identification at the Emergency Department and the systematic fall-related drugs assessment will be determined based upon time measurements and employment of personnel. Costs of medication use will be recorded in the study, and unit costs will be determined with information from the National Dutch Formulary [25].

Healthcare consumption, both fall and non-fall related, and patient costs will be recorded from the Hospital Information System for hospital care, and three-monthly questionnaires for other healthcare and patient costs. These will be supplemented with data on healthcare costs of injury from previous research [9]. The number of injuries prevented will be calculated with data recorded in the study, supplemented with epidemiological data on falls and injury risks.

Cost-effectiveness will be assessed by calculating the incremental cost-effectiveness ratio, defined here as the difference in average costs between medication assessments including withdrawal of fall-risk increasing drugs and 'care as usual' and by the difference in prevented fall-related injury. Secondary, a cost-utility analysis will be performed, *i.e*., as cost per Quality Adjusted Life Years (QALY). Policy makers and health economists have proposed that costs varying from €25,000 up to €75,000 per QALY may be considered as acceptable [37,38].

The QALY combines mortality and morbidity into a single number. The morbidity component is referred to as HRQoL and is based on a descriptive health-state measure. Because of a long track record in health economic analyses, the EQ-5D measure will be used for this purpose [28]. Furthermore, the lifetime health effects (cardiovascular events such as myocardial infarction, stroke, and mortality) due to possible increased cardiovascular risks (*i.e*., cardiac failure, rebound hypertension) will be calculated with existing models for cardiovascular disease risk management. In accordance with guidelines for differential discounting, effects will be discounted at a rate of 1.5% and costs at 4% per year [39].

Full blood for DNA isolation will be drawn during the first visit (5 mL). The blood will be stored at -80 degrees Celsius, until DNA-isolation will take place. After DNA isolation, polymorphisms (CYP1A2, CYP2C9, CYP2C19, CYP2D6, CYP2E1 en CYP3A4) will be analyzed using the TaqMan allelic discrimination assays on the ABI Prism 9700 HT sequence detection system. If needed, other polymorphisms will be added to the analysis.

### Follow-up

Patients will be followed for one year. After the first visit to the research outpatient clinic patients receive a Falls Calendar [33]. During a one-year follow-up period, the participant will be asked to record every week whether they have experienced a fall that week. The 3-monthly calendar sheet will be returned once per 3-months by mail. Cost-effectiveness will be measured using a cost-evaluation questionnaire. Participant can register the number of visits to physicians, therapists, day care centers, hospitalizations, adaptations of the living area, and the current living location (*e.g*., home or nursing home). The cost-evaluation questionnaire will be returned with the falls calendar at three, six, nine, and twelve months after the first visit to the research outpatient clinic. In case no calendar sheet or questionnaire is received, or when it is completed incorrectly, the calendar sheet or questionnaire will be completed by telephone.

During the last visit to the outpatient clinic, one year after the first visit, all physical performance tests are conducted, as well as questionnaires regarding medical history, drug use, quality of life, and fall risk profile. Adherence to the drug-use recommendations (complete withdrawal, lowering of dosage, or substitution) will be evaluated by reassessment of drug use as described above. Information of the participants regarding medical history and drug use will be verified by the General Practitioner and local pharmacist.

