### Procedure

All persons visiting the Emergency Department due to a fall receive care as usual for their injuries. Within two weeks following the Emergency Department attendance, patients are contacted by telephone with information about the study. All eligible study participants will receive written information about the study and all interested patients will receive an appointment for the research outpatient clinic. The visits to the outpatient clinic take place within two months after Emergency Department attendance. If the patient meets all eligibility criteria and no exclusion criteria are present at the research outpatient clinic, the patient will be asked to sign the Informed Consent Form before the study procedures take place. Patients who do not meet the inclusion criteria will be excluded. During the outpatient clinic visit a record is made of the falls risk profile (FRP), falls history, health-related quality of life (HRQoL) and physical performance are measured of all study participants. Furthermore, a geriatric assessment and a standardized medication assessment will take place. Eligible patients will be randomized to one of the treatment arms, the intervention group versus 'care as usual'. The aim in the intervention group will be to reduce fall-risk increasing drugs, and in the 'care as usual' group no (medication) change will be made. All included participants receive a Falls Calendar for reporting falls during a one-year follow-up period as well as a cost-evaluation form at three, six, nine and twelve months after the first research outpatient clinic visit. One year after the first visit, the study participants are invited for a final visit to the research outpatient clinic in order to reassess the FRP, falls history, HRQoL, and physical performance. Adherence to their medication is also evaluated. After the final visit to the outpatient clinic a brief letter concerning the study start and completion will be sent to the patient's General Practitioner. Table 1 shows the schedule of events of this study.

**Table 1 T1:** Schedule of events

	Screening	1^st ^visit	3 months	6 months	9 months	12 months
Telephone call	X					
Information package	X					
Informed Consent		X				
Randomization		X				
Baseline data		X				
EQ-5D		X				X
SF-12		X				X
FRP		X				X
Orthostatic hypotension test		X				X
Complications			X	X	X	X
Falls calendar			X	X	X	X
Healthcare consumption			X	X	X	X
ADL		X				X
Physical functioning (VAS)		X				X

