### Sample size calculation

A total number of 620 patients will be included in the study, 310 in the control group and 310 in the intervention group. Calculation of the required sample size is based on the assumption that the annual cumulative incidence of further falling is 50% without intervention [40], a 15% drop-out (including death) [11], drug withdrawal being possible in 50% of the participants in the intervention group and a 50% decrease of further falls among participants with successful withdrawal [18]. A single-sided test with an alpha level of 0.05 and a beta of 0.2 indicates that 310 patients in both groups is sufficient in order to detect a 25% decrease of respondents reporting further falls in the intervention group.

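### EQ-5D, SF-12 and Barthel at 12 months are tied to the clinic visit; the telephone completion rule should be extended to living participants who do not attend

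*Protocol article*

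**What the plan says.** Table 1 of the protocol article schedules EQ-5D, SF-12 and ADL (the Barthel Index) at the first visit and at 12 months, and at no time between.

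The Procedure section says that "the study participants are invited for a final visit to the research outpatient clinic in order to reassess the FRP, falls history, HRQoL". The Follow-up section puts the physical tests at that visit, "as well as questionnaires regarding medical history, drug use, quality of life, and fall risk profile". Barthel is not named in either sentence, but Table 1 gives it the same two time points and the Measurements section describes it under Quality of life.

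The falls calendar and the cost form are handled differently. The calendar is returned by mail, and "The cost-evaluation questionnaire will be returned with the falls calendar at three, six, nine, and twelve months". The next sentence is the rescue rule: "In case no calendar sheet or questionnaire is received, or when it is completed incorrectly, the calendar sheet or questionnaire will be completed by telephone". The final visit is taken up only in the paragraph after that.

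Adherence "will be evaluated by reassessment of drug use as described above". The method referred to, under Medication use, compares the packaging with data from the General Practitioner and local pharmacist. The Follow-up section repeats that verification for the final visit.

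HRQoL, compliance and QALY are secondary outcomes. The Costs section builds the QALY from mortality and EQ-5D.

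**The concern.** Participants enter able to walk independently and living in the community. Some may break a bone, move to a nursing home or become too frail to travel during the year. The article foresees such changes, since the cost form records hospitalizations and current living location. These participants can still report falls and costs by telephone, and hospital use comes from the Hospital Information System. Their quality of life is asked only at a visit they may be unable to make.

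Non-attendance could then be related to the falls and decline that the intervention is meant to change. If withdrawal prevents serious falls, more poor utilities may go unrecorded in the control arm and a benefit would be understated. If withdrawal does harm, the harm could be understated in the same way. Cost per QALY would combine costs from nearly everyone with 12-month utilities from attenders.

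**Working it through.** **1. What each item depends on**

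| Item | After baseline | Stated mode | Stated alternative |
|---|---|---|---|
| Falls calendar | 3, 6, 9, 12 months | mail | telephone |
| Cost-evaluation questionnaire | 3, 6, 9, 12 months | returned with the calendar | telephone |
| EQ-5D, SF-12 | 12 months | clinic visit | none |
| Barthel | 12 months | clinic visit, by inference | none |
| Drug use | 12 months | clinic visit | General Practitioner and pharmacist data, described as verification |
| Death, for the QALY | any time | no visit needed | not applicable |

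The rescue rule applies when a form is not received, which fits mailed items, and it directly follows the sentence on mailed items. The word questionnaire is not expressly limited to the cost form, but that is the natural reading.

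**2. How many participants**

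The article gives no figure for missing HRQoL, so there is none to reproduce. The sample size section allows 15% drop-out, deaths included:

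- 0.15 × 310 = 46.5 per arm, and 0.15 × 620 = 93 in total
- 310 × 0.85 = 263.5 per arm remaining

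The number alive but not attending is not given. If the whole 15% lacked a value, the standard error would grow by a factor √(1/0.85) = 1.085, about 8%. Part of that loss is death, which a telephone call does not recover.

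**3. Bias in mean utility if only attenders are analysed**

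Let m be the proportion of survivors in an arm without a value, and d the mean utility of attenders minus that of non-attenders. The true mean is (1 − m) × attenders + m × non-attenders, so the attenders' mean is too high by m × d. The bias in the difference, intervention minus control, is m_I × d_I − m_C × d_C.

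All values of d and all differences in m below are assumptions; the article gives neither.

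- Same m and same d in both arms: bias 0. With m = 0.15 and d = 0.1 to 0.3, each arm's mean is 0.015 to 0.045 too high, but the difference is unaffected.
- d = 0.2 in both arms, m differing by 0.03 to 0.05: 0.2 × 0.03 = 0.006 to 0.2 × 0.05 = 0.010.
- Wider case, m = 0.20 in control and 0.10 in intervention, d = 0.1 to 0.3: 0.10 × d = 0.01 to 0.03, against the intervention.

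**4. Bias in QALY**

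With baseline observed in everyone and linear interpolation over one year, an error in the 12-month value counts for half.

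- Main illustration: 0.006/2 to 0.010/2 = 0.003 to 0.005 QALY
- Wider case: 0.01/2 to 0.03/2 = 0.005 to 0.015 QALY

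At the article's €25,000 to €75,000 per QALY, the main illustration is worth 0.003 × 25,000 = €75 to 0.005 × 75,000 = €375 per patient.

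**5. Compared with sampling error**

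Assume an EQ-5D standard deviation of 0.2 to 0.3 (also not in the article) and 263.5 per arm. The standard error of the difference is SD × √(2/263.5), which is 0.017 to 0.026. A bias of 0.006 to 0.010 is then about 0.2 to 0.6 of one standard error.

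**The case against.** The strongest objection is that this is a condensed article. It says where the measurement is planned; it does not say that the clinic is the only route or that non-attenders are lost. A fuller protocol may have a procedure for them, and the handling of missing EQ-5D belongs in an analysis plan. No attenders-only analysis is specified, intention-to-treat is the stated principle, and entry criteria already exclude people unwilling to return or likely to be lost. Only secondary outcomes are touched: the first-named cost-effectiveness ratio uses prevented injuries, not QALYs.

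Much of this stands, and it limits the weight of the point. It does not remove it. The article is not silent on non-response: it states a rescue for two instruments and ties the others to attendance. This is data collection, not analysis. An imputation model could borrow from falls, costs and residence, but it cannot recover an EQ-5D that was never asked. The entry criteria address unwillingness and foreseeable problems, not later inability to travel.

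Three stronger readings are tempting, and the text does not support them:

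- A reader might infer that adherence too has no fallback. General Practitioner and pharmacist data are a named second source of drug use. What is unstated is whether they are used when the visit does not take place.
- A reader might infer that everyone who fared worst is missing from the QALY. Deaths can enter it without a visit; the gap concerns survivors.
- A reader might infer that the comparisons are biased. That needs non-attendance or utility deficits that differ between arms, and the article shows neither.

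**Conclusion.** The point holds for HRQoL and for the utility of survivors. As written, the only post-baseline EQ-5D, SF-12 and Barthel values depend on one clinic visit, while falls and costs do not. Loss of precision follows for any survivor who does not attend. Bias between arms is possible but not established: it is zero with equal non-attendance and equal deficit, and about 0.003 to 0.005 QALY under the assumed 0.2 deficit and 3 to 5 point difference. That is small against sampling error under the assumed standard deviation. The primary falls outcome is unaffected. This is a cheap improvement to data collection, not a flaw that threatens the trial's main result.

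**What to change.** In the Follow-up section, extend the telephone or mail completion rule to EQ-5D, SF-12 and Barthel at 12 months for every living participant who does not attend the final visit, and record the mode of completion. Add a sentence stating that the General Practitioner and pharmacy record, already retrieved for verification, is the source of 12-month drug use when the visit does not take place. Items that need measurement in person (the physical tests, grip strength and body weight for the Fall Risk Profile, and the orthostatic test) would still depend on attendance.

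The cost is two sentences and a few extra calls or mailings through a process already running. The downside is a mode difference for a minority of questionnaires, which the recorded mode allows the analysis to examine.

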### Sample size calculation

A total number of 620 patients will be included in the study, 310 in the control group and 310 in the intervention group. Calculation of the required sample size is based on the assumption that the annual cumulative incidence of further falling is 50% without intervention [40], a 15% drop-out (including death) [11], drug withdrawal being possible in 50% of the participants in the intervention group and a 50% decrease of further falls among participants with successful withdrawal [18]. A single-sided test with an alpha level of 0.05 and a beta of 0.2 indicates that 310 patients in both groups is sufficient in order to detect a 25% decrease of respondents reporting further falls in the intervention group.

### Statistical analysis

Data will be primarily analyzed according to the intention-to-treat principle. Patients with protocol violations will be followed up, and data will be recorded. Data will be analyzed with and without inclusion of patients with protocol violation. At baseline, differences in baseline characteristics will be compared between the intervention and control group in order to assess comparability between the two groups. Student's T-test (parametric numeric data), Mann-Whitney U-test (nonparametric numeric data) or Chi-square test (categorical data). Data will be presented as mean ± SD (parametric data) or medians and percentiles (non-parametric data).

The hazard ratio for falling will be calculated using a Cox-regression model. Herein, the time between the intervention (*i.e*., drug assessment/change or not) and the first and/or second fall will serve as the primary outcome measure. Fallers will be defined as those who will fall once or more during the one-year follow-up. Differences in cumulative incidence of falls will be analyzed using log-linear or Poisson regression, adjusted for over dispersion because of interdependence among the dependent variable (falls). Differences in adverse health effects between both trial arms will be assessed using Chi^2 ^testing. Several subgroups will be distinguished in order to examine whether the effect of the intervention depends upon sex, age, race and risk of future falls. Since healthcare costs per patient are typically highly skewed, non-parametric techniques will be used to derive a 95% confidence interval for the differences in distributions of the costs. In a sensitivity analysis the impact on cost-effectiveness of statistical uncertainty on the main study outcomes will be determined (uni- and multi-variable).

The association between genetic polymorphisms and falls history will be evaluated using a multivariate logistic regression analysis. A *p*-value of < 0.05 will be used as threshold for statistical significance.

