## Methods/Design

The study is designed as a multicenter RCT with a one-year follow-up period in the Netherlands. The Medical Ethics review board of the Erasmus MC, University Medical Center, approved the study protocol. The study started in October 2008. The flow chart is shown in Figure 1.

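### Baseline differences between randomised arms are to be significance-tested, while the Cox and fall-rate models are stated without the prognostic baseline variables already collected; pre-specified adjustment would add a modest amount of power

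*Protocol article*

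**What the plan says.** The Statistical analysis section of the protocol article states: "At baseline, differences in baseline characteristics will be compared between the intervention and control group in order to assess comparability between the two groups". It then lists Student's t, Mann-Whitney and chi-square tests by type of variable. The section ends with a general rule that a p-"value of < 0.05 will be used as threshold for statistical significance", and the baseline comparisons are not exempted.

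For the primary outcome it states: "The hazard ratio for falling will be calculated using a Cox-regression model". No covariate is named. The number of falls goes into a log-linear or Poisson model, where the only adjustment mentioned is for overdispersion. Sex, age and risk of future falls appear once in this section, as subgroup factors (together with race).

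The Procedure section and Table 1 show that the Fall Risk Profile is recorded at the first visit for all participants. The Quality of life section calls it validated, gives a range of 0 to 30, and says that a score of "11 and over indicates a high risk of recurrent falling (2 or more falls in the next 12 months".

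The Sample size calculation assumes 50% fallers without intervention, a 25% relative reduction, 15% drop-out and "A single-sided test with an alpha level of 0.05 and a beta of 0.2", giving 310 per arm.

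**The concern.** Under proper randomisation any baseline difference is due to chance, so a p-value for it tests a hypothesis known to be true. It also says nothing about whether the difference matters. A large imbalance in a weak predictor can be significant, while a moderate imbalance in a strong predictor is not. The text also gives no rule for what follows a significant difference, which leaves room for choosing covariates after seeing the data in a trial where patients and geriatricians are not blinded.

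Meanwhile the baseline variables most likely to explain who falls again have no stated place in the main comparison. If they are prognostic, a model that ignores them has less power than the same data allow, and a chance imbalance in fall risk is left in the estimate.

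**Working it through.** **Inputs.** From the Sample size calculation: fallers 50% and 50% × 0.75 = 37.5%; 310 per arm; 15% drop-out. Evaluable per arm: 310 × 0.85 = 263.5. The prognostic strength of the score is not given, so it is an assumed range.

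**The plan's own figure.** For two proportions with mean 0.4375 and difference 0.125, n = [z_α√(2 × 0.4375 × 0.5625) + z_β√(0.5 × 0.5 + 0.375 × 0.625)]² / 0.125².
- Two-sided: (1.96 × 0.7016 + 0.8416 × 0.6960)² / 0.015625 gives 247; with continuity correction 262; 262 / 0.85 gives 309. This matches 310.
- One-sided, as worded: 194, or 210 with correction; divided by 0.85 these give 229 and 248.

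The stated 310 therefore corresponds to a two-sided, continuity-corrected test. That mismatch is a separate matter. Here it only means that results are shown for both one- and two-sided tests.

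**Power without adjustment.** Implied hazard ratio: ln(0.625) / ln(0.5) = 0.678. Expected first falls: 2 × 263.5 × 0.4375 = 230.6. Power = Φ(½√230.6 × |ln 0.678| − z) = Φ(2.95 − z), which is 84% two-sided (z = 1.96) and 90% one-sided (z = 1.645).

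**Power with adjustment.** Simulated Cox models: 1,500 trials per setting, 264 evaluable per arm, exponential hazards, one standard-normal baseline score, marginal one-year risks held at 50% and 37.5%. Simulation error is about 1 point.

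| Assumed hazard ratio per SD | AUC | Two-sided 0.05, unadjusted → adjusted | Gain (points) | One-sided 0.05, unadjusted → adjusted | Gain (points) |
|---|---|---|---|---|---|
| 1.00 | 0.50 | 85.4% → 85.3% | −0.1 | 91.4% → 91.5% | 0.1 |
| 1.28 (e^0.25) | 0.60 | 83.7% → 85.8% | 2.1 | 90.9% → 92.1% | 1.2 |
| 1.49 (e^0.4) | 0.65 | 81.9% → 86.0% | 4.1 | 89.4% → 91.5% | 2.1 |
| 1.82 (e^0.6) | 0.71 | 83.7% → 89.4% | 5.7 | 89.9% → 93.2% | 3.3 |
| 2.23 (e^0.8) | 0.76 | 85.5% → 93.9% | 8.4 | 91.8% → 96.6% | 4.8 |

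A hazard ratio of 2.0 lies between the last two rows. A further run at 1.35, 1.65 and 2.0 per SD gave about 2, 3 to 4 and 5 to 8 points two-sided, and about 1 to 5 points one-sided. If drop-outs contribute follow-up until they leave, two-sided power is higher throughout but the gains are similar: 87.5% → 88.7%, 88.0% → 92.0% and 89.8% → 95.3% at the same three strengths (600 trials each; a 1,200-trial rerun of the first gave 86.5% → 87.0%).

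**Analytic check at 1.82 per SD.** The conditional hazard ratio is 0.650, so ½√230.6 × |ln 0.650| = 3.27. Φ(3.27 − 1.96) is about 90%, in line with the simulated 89.4%.

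**Shift in the estimate.** The mean estimated hazard ratio moves from 0.679 to 0.667 at AUC 0.65, and from 0.674 to 0.650 at AUC 0.71.

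**Baseline tests.** With k independent variables tested at 0.05, the chance of at least one false imbalance is 1 − 0.95^k: 40% for k = 10 and 64% for k = 20. Both k and independence are assumptions. The article lists many baseline measures but no count.

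**The case against.** The strongest objection is that a reader might infer that the primary Cox model will be run unadjusted. The article does not say so; it names no covariates. It condenses a fuller protocol, an analysis plan may exist, and covariate lists are commonly left there. This stands: adjustment is offered as a better method to fix in advance, not as the repair of a proven omission. For the same reason nothing is claimed here about stratifying by centre or about baseline adjustment of quality-of-life and mobility outcomes.

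Other stronger readings also fail.
- *The unadjusted hazard ratio is biased toward 1.* It is not. Marginal and conditional hazard ratios are different quantities in a Cox model, and the unadjusted one is a valid randomised comparison.
- *The score is a strong predictor of the primary outcome.* The article describes it for recurrent falls, two or more, whereas a faller here needs only one. All participants have already had a fall and take fall-risk increasing drugs, so discrimination may be weaker among them.
- *Fall risk is collected and ignored.* It is used to define subgroups.
- *The baseline tests will select covariates.* No sentence says so. Their stated purpose is comparability, and removing them alone changes no result.
- *Adjustment is free.* It needs no new data, but it changes the estimand and needs rules.

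It is also fair to say that unadjusted power already exceeds the planned 80%. What survives is that the named tests cannot serve their stated purpose, and that a better-specified model is available from data already collected.

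**Conclusion.** The point holds in limited form. Significance testing of baseline differences is stated and is uninformative. The fall models, as published, make no use of prognostic baseline variables that every participant has. Adjusting in advance would add about 0 to 8 points of power two-sided and about 0 to 5 points one-sided, for an assumed hazard ratio of 1.0 to 2.0 per SD of the score. If the score does not predict falls in this population, the gain is nil. These figures rest on proportional hazards, a normally distributed score entering linearly, and the article's own event rates and drop-out. The validity of the primary comparison is not in question; the issue is efficiency, and protection against covariates being chosen after the data are seen.

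**What to change.** - Pre-specify the Cox model and the fall-rate model as adjusted for baseline Fall Risk Profile (continuous), age and sex, and report the unadjusted results alongside.
- Replace the baseline tests with a descriptive table by arm, without p-values.
- State that baseline comparisons will not decide which covariates enter any model.
- Fix the functional form of the score and a rule for missing scores before analysis; the score includes handgrip strength and body weight, either of which may be unrecorded for some patients.
- State that the adjusted hazard ratio is a conditional effect.

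The cost is wording and these few rules. No extra patients, visits or data are needed.
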